## Abstract

**Introduction:**

The microcirculation is the physiological site of oxygen and substrate exchange. Its effectiveness during circulatory shock is vital for the perfusion of tissues, and has a bearing on subsequent organ function and prognosis. Microcirculatory dysfunction following traumatic haemorrhagic shock (THS) has been understudied compared with other pathologies such as sepsis. The aim of the MICROSHOCK study is to investigate changes seen in the microcirculation of patients following THS, and to assess its response to resuscitation. A greater understanding of the behaviour and mechanisms of microcirculatory dysfunction in this context may direct future avenues of goal-directed resuscitation for these patients.

**Methods and analysis:**

This multicentre prospective longitudinal observational study includes patients who present as an emergency with THS. Microcirculatory parameters are recorded using sublingual incident dark field microscopy alongside measurements of global flow (oesophageal Doppler and transthoracic echocardiography). Patients are enrolled into the study as soon as feasible after they arrive in hospital, and then at subsequent daily time points. Blood samples are taken for investigation into the mechanisms of microcirculatory dysfunction. Sequential Organ Failure Assessment scores will be analysed with microcirculatory parameters to determine whether they correlate with greater fidelity than more conventional, global circulatory parameters.

**Ethics and dissemination:**

Research Ethics Committee approval has been granted for this study (Reference: 14/YH/0078). Owing to the nature of THS, capacity for informed consent will be absent on patient enrolment. This will be addressed according to the Mental Health Capacity Act 2005. The physician in charge of the patient's care (nominated consultee) may consent on behalf of the patient. Consent will also be sought from a personal consultee (close relative or friend). After capacity is regained, the participant will be asked for their consent. Results will be submitted for publication in peer-reviewed journal format and presented at relevant academic meetings.

**Trial registration number:**

NCT02111109; Pre-results.

Strengths and limitations of this study
This study's main strength is that it will be the largest clinical investigation into the microcirculatory response to traumatic injury and haemorrhagic shock to date.The MICROSHOCK study will recruit from major trauma centres in London and Birmingham, the two largest cities in the UK.The study is limited by its observational nature. However, the key research question ‘Does the microcirculatory behaviour predict outcome better than global haemodynamic parameters?’ can be addressed using observational data.A further limitation is the heterogeneous nature of injury patterns in the UK trauma patient population. Such differences will be addressed during data analysis, and reported during the dissemination of the results. These differences will be much greater than those in animal studies. However, a clinical study allows us to translate what has been learnt from animal research into useful and clinically relevant knowledge.

## Background

Massive haemorrhage and associated shock is a leading cause of preventable death among casualties with severe traumatic injury, accounting for around 40–50% of all deaths.^1^
^2^ Despite significant improvements in treatment and mortality within this patient group, systemic inflammatory response, coagulopathy and subsequent multiple organ failure remain common.^3^ These issues can lead to prolonged periods of morbidity, critical care dependency and often death. Therapeutic interventions that attenuate these responses may lead to significant benefit for patients who have suffered traumatic haemorrhagic shock (THS).^3^

The microcirculation is of particular clinical importance during circulatory shock since it is this network of capillaries and other small vessels that perform the essential functions of delivering oxygen and substrates to cells. Traditionally, resuscitative strategies are guided by measurement of global haemodynamic parameters such as blood pressure and cardiac output. However, there may be a poor correlation between such global parameters and the appearance of the microcirculation.^4^
^5^ Microcirculatory parameters may also predict outcome better than more conventional global circulatory measurements in sepsis.^6^ Observational data suggest patients who can improve the state of the microcirculation in response to resuscitative fluid therapy have a better outcome than those who cannot.^7^
^8^

Incident dark field (IDF) video microscopy is a method of assessing the microcirculation that has been developed relatively recently for clinical and research.^9^ A light source is applied to the tissue, which illuminates the deep tissues within the target field. The reflected light from the deep tissues is captured and magnified before being received on a viewer. The selective wavelength of transmitted light is completely absorbed by both oxygenated and deoxygenated haemoglobin, and blood vessels therefore appear black. The technique is limited to organs that have a thin epithelial covering and that are accessible to a handheld probe, which in clinical practice has usually been the sublingual microcirculation. The device is small, portable and the technique non-invasive. Obtaining images with the device requires between 2 and 5 min and involves the use of a small, non-traumatic sublingual probe. The images produced by IDF microscopy require offline analysis and the ascription of objective values before they can be used. De Backer *et al*^10^ have standardised this approach.

Most clinical studies that examine the microcirculation have focused on sepsis,^7^
^11^
^12^ whereas studies relating to haemorrhagic shock are mostly limited to animal experiments, and have usually looked at controlled haemorrhagic shock rather than a complex traumatic injury model.^13–15^ One clinical study has examined the microcirculation after THS once the patients had been admitted to the intensive care unit (ICU), but did not gather data during the early phases of resuscitation.^16^ Although they share similarities, septic and haemorrhagic shock must be examined separately in a clinical context, so that their respective differences can be delineated, and unanswered questions can be addressed.

### Primary objective

The primary objective of the MICROSHOCK study is to examine the microcirculatory function in patients following THS, and to determine whether these parameters are superior to global haemodynamic parameters in the prediction of clinical outcomes.

## Methods

### Study design

This is a multicentre prospective longitudinal observational study that involves serial assessments of the sublingual microcirculation alongside measurements of global flow, volume status and blood pressure, determined from existing monitoring devices and using focused transthoracic echocardiography. In conjunction, data will be gathered relating to the patients physiology and resuscitation.

### Patient screening

All patients with a history of traumatic injury presenting to the emergency department (ED) at the study site hospitals will be screened by research staff. These sites are all UK Major Trauma Centres, and include (1) Kings College Hospital, London, UK; (2) The Royal London Hospital, London, UK; and (3) Queen Elizabeth Hospital Birmingham, Birmingham, UK. Patient details will be recorded in a screening log.

### Number of patients

A single pilot study demonstrated feasibility in the examination of the microcirculation following THS, and reported data for 18 patients.^16^ The current study will be the first to examine the microcirculation of patients with THS as soon as they have arrived in the ED. The MICROSHOCK study will enrol 60 patients in order to further investigate the microcirculation following THS, and form hypotheses that might direct future goal-directed interventions.

### Inclusion criteria

Adult patients with evidence of haemorrhagic shock exhibiting all of the following features:
Mechanism of injury consistent with blood loss;Intubated and ventilated;Serum lactate concentration >2 mmol/L recorded at any stage prior to admission to the ICU;Have received any blood products (eg, packed red blood cells (PRBC), fresh frozen plasma (FFP), cryoprecipitate, platelets) during the initial period of resuscitation, prior to admission to ICU, or are predicted to receive blood products during this timeframe in the opinion of the trauma team leader.

### Exclusion criteria

Patients with facial injuries, where access to the sublingual area would be problematic will be excluded. Patients with injuries deemed unsurvivable in whom the focus of care is palliation rather than active treatment are also ineligible for inclusion.

### Time points and techniques for data collection

Figure 1 outlines the techniques that will be utilised, samples taken and data collected at each time point. There are five main time points:
As soon as feasible after arrival in hospital (T1), and up to every 60 min until haemodynamically stable;On admission to ICU (D0);24 h after D0;48 h after D0;72 h after D0.

**Figure 1 BMJOPEN2015010893F1:**
[figure not shown]
Sampling and techniques. BP, blood pressure; ED, emergency department; GCS, Glasgow Comas Scale; ICU, intensive care unit; IDF, incident dark field; HR, heart rate; RR, respiratory rate.

Where feasible, and appropriate, further readings will be taken between the first and second time points. Data collection is stopped once the patient has been extubated.

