### Oesophageal Doppler

An oral oesophageal Doppler probe (Deltex Medical, Chichester, UK) will be inserted at the same time as acquisition of the first IDF images. The probe will remain in situ continuously for 72 h or until the patient is ready for extubation. The following data will be recorded: corrected flow time, stroke volume, cardiac output. Data obtained from this monitoring device will also be available for use to the patients’ attending clinicians if they wish.

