### Primary outcome

The primary outcome is the Sequential Organ Failure Assessment (SOFA) score at the D3 time point (72 h after admission to ICU), and will be recorded using information from the patients’ charts and laboratory results.

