### Secondary outcomes

Secondary outcomes include SOFA scores and multiorgan dysfunction score on days 1, 7 and 28 of hospital admission (if the patient is still an inpatient), mortality at 28 days, length of stay (LOS) in hospital, LOS in ICU, number of days of mechanical ventilation, thromboelastography parameters, arterial and venous blood gas parameters, and blood product requirements.

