### Safety

The chief investigator has overall responsibility for the conduct of the study including responsibility for safety. Individual investigators will be responsible for reporting all serious adverse events (SAEs) and adverse events (AEs) to the chief investigator. There are no reported AEs associated with the use of IDF imaging in the published literature, and the risk of harm occurring to a study participant as a direct result of undergoing IDF imaging is close to zero. An example of an attributable AE would be a sublingual haematoma following IDF microscopy. SAEs will include death, any event which poses a threat to life, prolongs hospital stay or produces significant disability. Given the nature of the study population, it is anticipated that such features will be relatively common as part to the pathological process of trauma, but not as a result of participation in the study. The chief investigator will review all events to decide if there is any causal link. If this is the case action will be taken in accordance with the principals of ICH GCP.

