### Statistical analysis

Normally distributed data will be presented as mean and SD, and non-normally distributed data will be presented as median and IQR. For comparison, patients will be dichotomised according to day 3 SOFA score into those with a score ≥6 versus those with SOFA score <6. The score of 6 has been chosen due to its prognostic relevance^18^ and previous utilisation as an end point for haemorrhagic trauma patients.^16^ Further analysis will be conducted according to the change in SOFA scores between days 1 and 3, so that patients are dichotomised into SOFA score ‘improvers’ and ‘non-improvers’. This approach has also been used as an end point for haemorrhagic trauma patients.^19^ Groups will be compared using a two-tailed t test for normally distributed data and the Mann-Whitney U test for non-normally distributed data. A p value of <0.05 will be considered statistically significant.

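### The primary outcome, SOFA at 72 h after ICU admission, has no value for a patient who dies earlier, and neither planned comparison gives these patients a group; the extubation stop rule also needs its scope stated

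*Protocol article*

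**What the plan says.** All references are to the protocol article.

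- **Primary outcome:** "The primary outcome is the Sequential Organ Failure Assessment (SOFA) score at the D3 time point (72 h after admission to ICU"). The score "will be recorded using information from the patients’ charts and laboratory results".
- **Statistical analysis:** "patients will be dichotomised according to day 3 SOFA score into those with a score ≥6 versus those with SOFA score <6". A second grouping uses the change in SOFA from day 1 to day 3. Groups are compared by t test or Mann-Whitney U test. No group is named for a patient without a day 3 score.
- **Time points and techniques for data collection:** measurement starts as soon as feasible after arrival in hospital (T1). The 72 h clock starts only at ICU admission (D0).
- **Safety:** SAEs include death, threat to life, prolonged stay and significant disability, and "it is anticipated that such features will be relatively common as part to the pathological process of trauma".
- **Capacity and consent:** the data of patients who die are kept, subject to the consultee's wishes.
- **Text under Figure 1:** "Data collection is stopped once the patient has been extubated".
- **Oesophageal Doppler:** "The probe will remain in situ continuously for 72 h or until the patient is ready for extubation".
- **Secondary outcomes:** "SOFA scores and multiorgan dysfunction score on days 1, 7 and 28 of hospital admission (if the patient is still an inpatient"), and also "mortality at 28 days, length of stay (LOS) in hospital, LOS in ICU, number of days of mechanical ventilation".

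**The concern.** A patient who dies before D3 cannot have a D3 SOFA score. One who dies in the emergency department or in theatre never reaches D0, so for that patient the D3 time point does not exist. Both planned comparisons need the D3 score. The article keeps these patients' data and counts 28-day mortality, but gives them no place in the primary comparison.

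The loss depends on the outcome itself. The missing patients would belong to the worse group, so the group that remains is less severely ill than the real one and the contrast in the marker shrinks. Enrolling more patients would restore precision but would not remove this attenuation. The primary objective, whether microcirculatory parameters predict outcome better than global haemodynamics, would then be answered only among patients who survive to 72 h. Early enrolment, which the article presents as the study's novelty, increases the exposure to such deaths.

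The extubation sentence is a second and smaller matter. It does not say which data stop, while other sections require outcomes that can fall after extubation.

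**Working it through.** **1. Is there a rule for early death?** The primary outcome is defined at one time point, with no alternative value. The ≥6 v <6 split and the improver split both use the day 3 score. The secondary SOFA scores are limited to patients still in hospital, so availability was considered there, but the primary outcome has no matching provision. Nothing in the article assigns a patient who dies before 72 h to a group.

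**2. What would dropping these patients do?** The article gives no power calculation, effect size, SD or death rate, so there is no figure of its own to reproduce. From the article: n = 60, two-sided alpha 0.05, two groups, t test. Assumed: correlation 0.40 between marker and severity (both standard normal, the marker's sign set so that higher means worse), a cut at the median, and early death in d = 5%, 10% or 20%.

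If the deaths are exactly the most severe patients, with c = Φ⁻¹(1 − d):

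- mean severity in the lower group = −φ(0)/0.5 = −0.798
- mean severity in the upper group = [φ(0) − φ(c)]/(0.5 − d)
- marker difference = 0.40 × (upper mean − lower mean)
- marker variance within a group = 0.16 × (severity variance in that group) + 0.84
- noncentrality = (difference/pooled SD) × √[n₁n₂/(n₁ + n₂)], with power from the noncentral t distribution on n₁ + n₂ − 2 df

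| Early deaths dropped | n₁ / n₂ | Upper mean | Marker difference | Pooled SD | Standardised difference | Noncentrality | Power |
|---|---|---|---|---|---|---|---|
| 0 | 30 / 30 | 0.798 | 0.638 | 0.948 | 0.67 | 2.61 | 0.73 |
| 3 (5%) | 27 / 30 | 0.657 | 0.582 | 0.941 | 0.62 | 2.33 | 0.63 |
| 6 (10%) | 24 / 30 | 0.559 | 0.543 | 0.939 | 0.58 | 2.11 | 0.54 |
| 12 (20%) | 18 / 30 | 0.397 | 0.478 | 0.938 | 0.51 | 1.71 | 0.39 |

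Simulation of the same model (20,000 replicates) gives 0.72 with nobody lost, then 0.62, 0.54 and 0.38. If death follows severity only loosely (noise of SD 0.7 added to the removal rule), the values are 0.65, 0.58 and 0.47. If deaths stay in and are counted in the worse group, power is about 0.71–0.73 at every rate. With the Mann-Whitney test, power starts at about 0.70 and falls to 0.60–0.37 over the same death rates; worst-rank handling keeps 0.68–0.70.

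**3. What does the extubation sentence cover?** Read literally, it stops everything, which conflicts with SOFA at 72 h, SOFA on days 7 and 28, length of stay and 28-day mortality. The Doppler section foresees extubation before 72 h, so the conflict can arise in practice. Against the literal reading, the SOFA score needs neither tube nor probe, the later outcomes are explicitly planned, and the sentence directly follows one about taking further readings. Bedside measurement is the natural scope.

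**The case against.** **The analysis plan may deal with death.** It is not shown, and the handling of missing values is commonly left to it. This has weight for methods of imputation. But the score is not merely unobserved here; it does not exist. Counting death as part of the outcome changes the primary outcome, and that is fixed in the protocol.

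**Early deaths may be few.** Patients with unsurvivable injuries under palliation are excluded, and the Safety statement covers prolonged stay and disability as well as death, with no rate for death before 72 h. This stands. The direction of the effect is established, but its size is not.

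**The study claims no power.** The 60 patients are meant to generate hypotheses. This also stands, and the power figures only give scale. Attenuation of the estimate matters in a hypothesis-generating study too.

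**A stronger reading is tempting:** that the primary outcome is lost at both ends of severity, so that results describe only patients alive and still ventilated at 72 h. The documents do not support it. SOFA comes from charts and laboratory results, and outcomes after extubation are planned. What extubation does remove is later imaging and Doppler readings. Nor does the article say that deaths are excluded; their omission follows from groups defined by a score they cannot have.

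**Conclusion.** The point holds for deaths before D3. As written, the primary outcome and both comparisons leave out the patients with the worst result, and the marker–outcome association is attenuated. Under the stated assumptions the standardised difference falls from 0.67 to between 0.62 and 0.51 when 5–20% die early and death follows severity exactly. Power falls from about 0.72 to between 0.65 (5%, loose link) and 0.38 (20%, exact link). The correlation, the cut, the death rates and the link between death and severity are all assumptions. So is the idea that the marker relates to severity in those who die as it does in the others, which the power retained under the fix depends on. The attenuation can affect microcirculatory and global predictors alike, and the documents do not show which would suffer more.

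On extubation, the conflict in wording is real, but the loss of D3 scores is only a risk, should any of the three sites follow the sentence literally.

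**What to change.** 1. **Text under Figure 1, reconciled with Primary outcome and Secondary outcomes.** State that the extubation stop applies to bedside imaging, Doppler and related readings. State that D3 SOFA is taken from charts and laboratory results for every enrolled patient alive at 72 h, extubated or not.
2. **Primary outcome and Statistical analysis.** Classify death before D3, including death before ICU admission, in the ≥6 group and as a non-improver, and give it the worst rank in any rank-based analysis. Report the number of such deaths, and show the survivors-only comparison as a sensitivity analysis.

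The cost is a few sentences and no new procedure, since SOFA already comes from routine records. The real downside is that the primary outcome becomes a composite of death and SOFA, which is less specific to organ dysfunction. The survivors-only analysis lets readers see how much the deaths contribute.

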### Demographic and resuscitation data

The following baseline (hospital admission) demographic and physiological data will be collected from study participants and recorded in an electronic database on a secure encrypted computer used only for research purposes. All data in this log will be anonymised and assigned a sequential study number.
Demographic details (age, gender, ethnicity);Mechanism of injury;Injury Severity Score (ISS);Admission systolic blood pressure (SBP), respiratory rate and Glasgow Comas Scale (GCS; to calculate Trauma and Injury Severity (TRISS) score);Administered prestudy blood products and intravenous fluids;Timings from injury to start of prehospital resuscitation, ED resuscitation and operating theatre-based resuscitation;Nature of initial surgical procedures and treatments.

### Acquisition of IDF images

The investigator will obtain video clips of the sublingual microcirculation using an IDF videomicroscope (Cytocam, Braedius Medical B.V., Huizen, The Netherlands). In accordance with international consensus criteria for assessing the microcirculation, enough video will be recorded to enable at least three (and preferably five) ×10 s video clips to be obtained at each time point. Because the microcirculation can demonstrate considerable heterogeneity, particularly in shock states, images will be acquired from different sites within the sublingual area. When acquiring images, investigators should actively seek to minimise pressure artefact by observing flow in medium and large vessels. The image should be stabilised with minimal movement artefact. Light intensity and focus should be optimised. Individual video sequences will be exported from the image acquisition software as DV-AVI files.

### Acquisition of transthoracic echo images

Subcostal and apical five-chamber windows will be obtained. The inferior vena cava will be visualised in M mode, and the minimum and maximum diameters across the respiratory cycle recorded. The left ventricular outflow tract (LVOT) will be visualised and a pulsed wave Doppler signal acquired. The LVOT velocity time integer (VTi) and the degree of variation across the respiratory cycle will both be recorded.

